### Interventions

2.5

All the acupuncturists have obtained the doctor qualification certificate and have certain clinical experience. At the same time, before the start of the study, all treating physicians should undergo systematic training to ensure the consistency of operation. During the treatment process, each patient will be treated by the same acupuncturist throughout the entire procedure.

An auxiliary device designed by our team will be used during the acupuncture procedure in order to achieve a single-blind effect, which has passed the national utility model patent (patent number: ZL202121352221.7), and the article introducing the device has been published in the journal of Chinese Acupuncture & Moxibustion (15). This new auxiliary acupuncture device includes an acupuncture device and a placebo acupuncture device with exactly the same appearance, which consists of a base sticking to the skin and a sleeve. The base of the acupuncture device is hollow, while the placebo acupuncture device is sealed by a bonding layer (Figure 2). A flat head needle (Tianxie, Suzhou Medical Appliance Factory, Suzhou, China; 0.30 mm × 10 mm) (Figure 3) will be used for the procedure. The acupuncturist can adjust the sleeve according to the insertion angle of needles (Figure 4).

**Figure 2 fig2:**
[figure not shown]
The placebo acupuncture device and the acupuncture device.

**Figure 3 fig3:**
[figure not shown]
The flat head needle (40 mm, 25 mm real needle and 10 mm sham needle).

**Figure 4 fig4:**
[figure not shown]
The angle of the sleeve (needle at 90-degree and 15-degree).

#### Acupuncture group

2.5.1

Patients in the acupuncture group will receive 20 sessions of acupuncture (four times a week for 5 weeks), during which the original effective dose of anti-Parkinson’s disease drugs will be maintained. If there is a need to increase or decrease the dose under special circumstances, the change will be recorded in the case report form. Acupuncture points of the acupuncture group include Si Shen Zhen (Four acupoints, consisting of GV21, GV19, and next to GV20 1.5 cun bilateral), Shen Ting (GV24), Yin Tang (GV29), Su Liao (DU25), Shen Men (HT7) (bilateral), San Yin Jiao (SP6) (bilateral), Hegu (LI4) (bilateral), and Taichong (LR3) (bilateral). The positioning of Si Shen Zhen is in accordance with the “Application of Jin San Zhen acupoint Group” (16), and other acupoints are in accordance with the National Standard of the People’s Republic of China’s (GB/T 12346–2006) standard (17). Acupuncture will be processed with disposable, sterile steel needles (Tianxie, Suzhou Medical Appliance Factory, Suzhou, China; 0.25 × 25 mm, 0.25 × 40 mm). Patients will wear the blindfold throughout the treatment. After routine skin disinfection, the acupuncturist will affix the acupuncture device (Guangzhou Suixin Medical Equipment Co., LTD.) to the acupoint skin. 0.25 × 25 mm acupuncture needles will be used for Si Shen Zhen, Shen Ting (GV24) and Yin Tang (GV29) with a 15-degree angle. 0.25 × 40 mm acupuncture needles will be used for Su Liao (DU25), Shen Men (HT7) (bilateral), San Yin Jiao (SP6) (bilateral), Hegu (LI4) (bilateral), and Taichong (LR3) (bilateral) with a 90-degree angle. The acupuncture needle is inserted through the sleeve and the perforated base into the skin. The location of each acupoint is shown in Table 1 and Figure 5. The needle will be retained for 30 min.

**Table 1 tab1:** The location of each acupoint.

Acupoint	Location
Si Shen Zhen	Four acupoints, consisting of GV21, GV19, and next to GV20 1.5 cun bilateral
Shen Ting	On the head, 0.5 cun directly above the midpoint of the anterior hairline.
Yin Tang	On the head, in the depression between the medial ends of the two eyebrows.
Su Liao	On the face, at the tip of the nose, in the exact center.
Shen Men	In the anterior wrist region, at the ulnar end of the distal wrist crease, on the radial side of the tendon of the ulnar flexor muscle of the wrist.
San Yin Jiao	On the medial side of the leg, 3 cun above the tip of the medial malleolus, posterior to the medial border of the tibia.
Hegu	On the dorsum of the hand, between the 1st and 2nd metacarpal bones, at the midpoint of the radial side of the 2nd metacarpal bone.
Taichong	On the dorsum of the foot, in the depression between the 1st and 2nd metatarsal bones, at the junction of the two bones.

**Figure 5 fig5:**
[figure not shown]
The location of each acupoint.

#### The placebo acupuncture group

2.5.2

Patients in the acupuncture group will receive 20 sessions of placebo acupuncture using sham acupuncture needles (four times a week for 5 weeks), during which the original effective dose of anti-Parkinson’s disease drugs will be maintained. If there is a need to increase or decrease the dose under special circumstances, the change will be recorded in the case report form. The acupuncture points of the placebo acupuncture group will be the same as those of the acupuncture group. Patients will wear the blindfold throughout the treatment. After routine skin disinfection, the acupuncturist will affix the placebo acupuncture device (Guangzhou Suixin Medical Equipment Co., LTD.) to the acupoint skin. The acupuncturist adjusts the sleeve according to the insertion angle of needles. The flat head needle (Tianxie, Suzhou Medical Appliance Factory, Suzhou, China; 0.30 mm × 10 mm) will be used for the procedure, and will be inserted through the cannulas to make patients feel slightly needled. The needle will be maintained for 30 min.

### Outcome measure

2.6

General information of the participants, including name, age, sex, disease duration, education, Levodopa-equivalent dose, will be collected before the study begin. Primary outcome measure will be the Montreal Cognitive Assessment Scale (MoCA). The secondary outcome will be the Mini-Mental State Examination (MMSE), Unified Parkinson’s Disease Rating Scale Motor Examination (UPDRSIII), serum neurofilament light polypeptide (NfL) and serum glial cell-derived neurotrophic factor (GDNF). Serological indicators will be measured by enzyme-linked immunosorbent assay (ELISA). The schedule of the outcome measurements is shown in Table 2.

**Table 2 tab2:** Schedule of enrollment, intervention, assessment and safety.

Study period								
Time point (Week)	−1	0	1	2	3	4	5	25
Enrollment								
Eligibility screen	×							
Informed consent	×							
Randomization		×						
Allocation		×						
Intervention								
Acupuncture								
Placebo Acupuncture								
Assessments								
MoCA		×					×	×
MMSE		×					×	×
UPDRSIII		×					×	×
NfL		×					×	
GDNF		×					×	
Safety								
Vital signs		×		×			×	×
Adverse events			×	×	×	×	×	×

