### Sample size

2.2

Aligned with the study’s objective, Montreal Cognitive Assessment Scale (MoCA) was chosen as the primary outcome. According to the results of previous experiments and literature review (13, 14), the mean and standard deviation of MoCA scale in PD-MCI patients received acupuncture combined with anti-PD drug treatment were 25.32 and 4.34, while there were 21.48 and 4.44, respectively, in PD-MCI patients who received sham acupuncture combined with anti-PD drug treatment. PASS V.15.0 (NCSS, Kaysville, UT, United States) was used to calculate the sample size. We set 90% for power level and 5% for two-sided significance level. It was estimated that there were about 29 patients in each group, and considering the dropout rate of 20%, the total sample size needed for study is 72, with 36 patients in each group.

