### Randomization

2.3

Subjects with PD-MCI who met the inclusion and exclusion criteria will be randomized using a simple randomization method in a 1:1 ratio into the acupuncture group and the placebo acupuncture group. Random sequence will be generated by a third party who do not participate in the study using SPSS Statistics 26.0 (IBM SPSS Statistics Inc., Chicago, United States).

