### Follow-up

2.8

Patients will be followed up 6 months after the end of treatment. The outcomes scales will be assessed to evaluate the long-term efficacy of acupuncture.

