### Statistical analysis

2.10

In this study, IBM SPSS Statistics 26.0 statistical software will be used to analyze the collected clinical data. Shapiro–Wilk will be used to test the normality before statistical analysis. Counting data is expressed as a percentage using a chi-square test. The measurement data meeting the normal distribution will be represented by mean ± standard deviation, while those not meeting the normal distribution will be represented by quartile. The independent sample t test will be used to compare the two groups with normal distribution and homogeneous variance, and the Mann–Whitney U test will be used to compare the two groups with non-normal distribution. The comparison difference before and after treatment will be treated by paired sample t test with normal distribution, and Wilcoxon rank sum test with abnormal distribution. The two groups of repeated measurement data do not meet the normal distribution of the generalized estimation equation, the simple effect in the group will be analyzed by Friedman test. Two-sided test will be applied uniformly in this study, and *p* ≤ 0.05 will be the standard of statistical significance.

To evaluate the clinical relevance of the findings, we will perform a responder analysis based on the minimal clinically important difference (MCID) for the MoCA. Based on previous literature in cognitive impairment (21), a change of ≥1.22 points on the MoCA scale will be considered clinically meaningful. Participants who show an improvement of ≥1.22 points from baseline to post-treatment will be classified as ‘responders’. The difference in the proportion of responders between the study groups will be compared using a Chi-square test, with a *p*-value < 0.05 considered statistically significant.

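### MoCA is named as the primary outcome, but no visit and no deciding test is fixed; if success may be claimed at week 5 or week 25, the false-positive rate is about 7–10%, not 5%

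*Protocol article*

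**What the plan says.** All references are to the protocol article.

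- **Primary outcome (2.6, 2.6.1.1).** "Primary outcome measure will be the Montreal Cognitive Assessment Scale (MoCA"). Section 2.6.1.1 describes the scale. Neither section attaches a visit or a deciding comparison.
- **Schedule (Table 2).** MoCA is marked at weeks 0, 5 and 25.
- **Timing wording (abstract; end of 2.6.2.2).** The scales are to be assessed before and after treatment. No visit is called primary.
- **Follow-up (2.8).** "The outcomes scales will be assessed to evaluate the long-term efficacy of acupuncture".
- **Sizing (2.2).** "We set 90% for power level and 5% for two-sided significance level". The calculation rests on one MoCA comparison, and its visit is not stated.
- **Tests (2.10).** The section lists between-group t or Mann–Whitney tests, paired before–after tests, methods for repeated measurements and a responder test. "Two-sided test will be applied uniformly in this study", and the same sentence sets p ≤ 0.05 as the general standard.
- **Responder analysis (2.10).** A MoCA gain of at least 1.22 points from baseline to post-treatment counts as response. "The difference in the proportion of responders between the study groups will be compared using a Chi-square test", with its own criterion of p < 0.05. Its stated purpose is clinical relevance.

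The secondary outcomes listed in 2.6 are MMSE, UPDRSIII, NfL and GDNF. Week-25 MoCA and the responder analysis are not among them.

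**The concern.** The efficacy conclusion rests on MoCA. The trial is sized as if one MoCA test at 5% decides it, but the plan provides between-group MoCA comparisons at two visits plus a responder comparison, each read against 0.05, with no order among them.

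Two things are at stake. First, if a significant result at either visit can be reported as success on the primary outcome, the error rate behind that claim is higher than the level used for sizing. Second, if week 5 and week 25 disagree, the plan does not say which result answers the trial's question.

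The visit at which the primary outcome is judged is part of the endpoint's definition and belongs in the protocol. Section 2.10 is detailed enough to fix the tests, the threshold and a responder cut-off, so the gap is not just a product of condensing a longer document.

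**Working it through.** **Inputs from the protocol article**
- Means and SDs (2.2): "were 25.32 and 4.34, while there were 21.48 and 4.44"
- Two-sided level 0.05 and power 0.90 (2.2)
- 29 evaluable per arm (2.2), then "considering the dropout rate of 20%, the total sample size needed for study is 72, with 36 patients in each group"
- 1:1 allocation (2.3)
- MoCA entry range 18–25 (2.1.1)
- Responder cut-off 1.22 (2.10)

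**Assumption, not in the documents:** the correlation ρ between MoCA scores at different visits. A range of 0.3 to 0.9 is shown.

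**Step 1: reproduce the plan's figure.**
- Difference = 25.32 − 21.48 = 3.84.
- Pooled SD = √[(4.34² + 4.44²)/2] = 4.39.
- The exact two-sample t test (noncentral t) at two-sided 0.05 has power 89.5% with 28 per arm and 90.5% with 29 per arm.

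So 29 per arm is reproduced, for a single test at 5%. Dropout: 29/0.8 = 36.25. The plan uses 36; rounding up would give 37, which is immaterial here.

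**Step 2: two visits, either of which may be claimed.** With no true effect, the two test statistics have approximately correlation ρ. The chance of at least one significant result is 1 − P(|Z₁| < 1.96 and |Z₂| < 1.96).

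| ρ | Either visit significant |
|---|---|
| 0 (independent) | 1 − 0.95² = 9.75% |
| 0.3 | 9.5% |
| 0.5 | 9.1% |
| 0.7 | 8.3% |
| 0.9 | 7.0% |

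**Step 3: check by simulation and add the responder test.** Each setting used 20,000 trials with no true effect, 29 per arm, whole-number MoCA scores capped at 30, t tests at weeks 5 and 25, and the week-5 responder chi-square test. ρ was 0.3, 0.5, 0.7 and 0.9.

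The responder test uses the baseline score, so the baseline spread matters. Scores confined to 18–25 cannot have an SD above (25 − 18)/2 = 3.5. The second and third rows therefore confine baseline to that range, with SD about 1.9 (an assumption).

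| Setting | Week 5 alone | Either visit | Either visit or responder |
|---|---|---|---|
| SD 4.4 at all visits | 4.8–5.0% | 7.2–9.5% | 11.4–13.1% |
| Baseline within 18–25, later SD 4.39 | 5.1–5.2% | 7.3–9.8% | 10.1–12.5% |
| Baseline within 18–25, later SD 3.0 | 4.9–5.1% | 7.2–9.7% | 11.0–13.0% |

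The two-visit figure barely depends on the baseline assumption. A single week-5 test holds 5%.

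**Step 4: the cost of the alternative.** If both visits were to count, each tested at 0.025:
- power with 29 per arm falls to 84.5%;
- 34 evaluable per arm are needed for 90%;
- 34/0.8 = 42.5, so 43 per arm and 86 in total.

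**The case against.** The best reply is that the article already points to week 5. The abstract and Section 2.6.2.2 speak of assessment before and after treatment. The later visit has its own section and its own purpose, long-term efficacy. The responder analysis is introduced to interpret findings, not as another route to success. On this reading there is one main assessment, a follow-up and a supportive analysis.

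Much of this stands. Week 5 is the natural reading, and the two visits are not presented as co-primary. But week 25 is also after treatment, no sentence makes week 5 decisive, and neither week-25 MoCA nor the responder analysis is labelled secondary. An inference, however reasonable, does not bind the analyst once results are known.

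Two stronger readings are tempting, and the documents do not support them.

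- *A reader might infer that the plan does exceed its stated 5%.* The excess arises only if success may be claimed on any of these tests, and no sentence says that it may. The 5% in Section 2.2 is the level of one sizing comparison, not a promise covering all tests.
- *A reader might count free choice between raw score and change from baseline as further chances of success, giving a still higher rate.* Nothing grants that choice, and score versus change is commonly left to the analysis plan. Such a calculation also depends on the baseline SD. Taking it as 4.39, as at the later visits, is impossible given the 18–25 entry range.

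The paired before–after tests are not counted either, because they do not compare the groups.

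**Conclusion.** The point holds as an unfixed primary endpoint. Sections 2.6 and 2.10 name MoCA but settle neither the visit nor the deciding test, while efficacy is assessed on it at two visits, each at 0.05.

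If either visit may carry the primary claim, the false-positive rate is about 7–10% against the 5% used for sizing. If the responder test could also be claimed, it is about 10–13%. The responder role is the weaker part, given its clinical-relevance purpose, but the two visits alone already exceed 5%.

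Both ranges rest on the assumed between-visit correlation of 0.9 to 0.3 and on the condition that any of these results may be claimed. The text does not grant that licence, but it does not exclude it. The change is worth making: it protects the main conclusion and costs very little.

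**What to change.** In Sections 2.6.1 and 2.10, state that:

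1. the primary endpoint is MoCA at week 5, the end of treatment;
2. it is tested once, between groups, at two-sided 0.05, in a model adjusted for baseline MoCA;
3. MoCA at the follow-up visit is secondary and the MoCA responder analysis is supportive, and neither can establish efficacy if the week-5 test fails.

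Naming a single test is what holds the 5% level. The baseline adjustment replaces the unadjusted t test and settles score versus change, since with baseline in the model both give the same treatment effect. Baseline MoCA is already collected. The same edit should give the follow-up visit one date: Table 2 puts it at week 25, which is 20 weeks after week 5, while Section 2.8 says six months after treatment ends.

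The cost is a few sentences, with no extra data or patients. The sizing already assumes one test at 5%, so the total stays at 72. The small downside is that a benefit seen only at follow-up would not count as success on the primary outcome.

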#### Primary outcome

2.6.1

##### The Montreal cognitive assessment scale (MoCA)

2.6.1.1

The MoCA has a certain sensitivity to screening PD-MCI, and the content of the scale is divided into 8 cognitive domains, including visuospatial and executive, naming, memory, attention, language, abstract ability, delayed recall, and orientation. The total score is 30 points. A score above 26 is normal, and a score between 18 and 25 refers to mild cognitive impairment. If when using this table, Add 1 point as correction when patients have less than 12 years of education.

#### Secondary outcomes

2.6.2

##### Mini-mental state examination (MMSE)

2.6.2.1

MMSE includes five cognitive areas of orientation, memory, attention and calculation, recall ability, and language ability. The total score is 30, and the score between 21 and 26 is considered mild cognitive impairment.

##### Unified Parkinson’s disease rating scale motor examination (UPDRSIII)

2.6.2.2

The UPDRS is a commonly used scale for the overall evaluation of PD patients and consists of four parts. UPDRSIII mainly evaluates the motor function of the patients. There are 14 items in total, the highest score of each item is 4 points, and the total score is 56 points. The higher the score, the more serious the motor symptoms of PD patients.

The above scales will be assessed before and after treatment.

##### Blood serum index

2.6.2.3

Cognitive impairment in PD is associated with dysfunction of a variety of neurotransmitter systems, including acetylcholinergic, dopaminergic, norepinephrine and 5-hydroxytryptaminergic. When the axons of nerve cells are damaged, they release serum neurofilament light polypeptide (NfL) into the cerebrospinal fluid and eventually into the blood (18). Serum glial cell-derived neurotrophic factor (GDNF) promotes the survival of dopaminergic (DA) neurons in the substantia nigra. GDNF may act in combination with neurotransmitters (HVA, 5-HT, GABA and Ach) to affect attention, memory and executive function in PD-MCI patients (19). Therefore, NfL and GDNF levels can reflect the activity of brain neurons, and NfL and GDNF can be used as biomarkers related to cognitive function.

Serum concentrations of NfL and GDNF will be measured before and at the end of treatment using enzyme-linked immunosorbent assay (ELISA), which follows the kit instructions strictly. Both ELISA kits will be provided by Jiangsu Enzyme Free Industrial Co., LTD.

### Safety evaluation

2.7

During the implementation of the study, adverse events of acupuncture, such as infection, bleeding, fainting, broken needles and subcutaneous hematoma will be handled promptly and recorded in the Adverse Event record Form. In case of serious adverse events, acupuncture treatment will be stopped and timely treatment measures will be carried out immediately. We will report to the Ethics Committee of the First Affiliated Hospital of Guangzhou University of Chinese Medicine at the same time. All adverse events will be classified and reported following CONSORT harm guideline (20).

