**Objective:**

This randomized, single-blind clinical trial aims to evaluate the efficacy and safety of acupuncture for PD-MCI. To improve the credibility of acupuncture research evidence through employing a sham acupuncture device as a control.

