### Blinding

2.4

To ensure the objectivity and accuracy of the results, this study adopts the single blind method to blind the subjects and the efficacy evaluator. Due to the limitations of needle operation, it is impossible to blind the operating physician, so the efficacy evaluator is a third party independent of the treatment operation and grouping to avoid subjective bias of the researcher. During the treatment, both groups of participants will be required to wear an eye mask to ensure the implementation of the blind method. At the end of the study, the blind will be uncovered and the participants will be informed of their group and acupuncture method.

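### The adverse event recording rule is tied to acupuncture-related events, at odds with the plan's own all-events reporting and Table 2, so capture could differ between real and sham arms

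*Protocol article*

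**What the plan says.** The Abstract (Objective) makes safety an aim alongside efficacy: the trial "aims to evaluate the efficacy and safety of acupuncture for PD-MCI".

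Three places bear on which adverse events are collected:

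- **Section 2.7, first sentence (recording).** "adverse events of acupuncture, such as infection, bleeding, fainting, broken needles and subcutaneous hematoma will be handled promptly and recorded"; the place of entry is a dedicated adverse event form. The events are qualified by acupuncture, and the five examples are illustrative.
- **Section 2.7, last sentence (reporting).** "All adverse events will be classified and reported following CONSORT harm guideline". There is no qualifier by cause.
- **Section 2.6, Table 2 (schedule),** titled "Schedule of enrollment, intervention, assessment and safety". An adverse events row is marked at weeks 1, 2, 3, 4, 5 and 25. It is one row for both arms and is not limited by cause.

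Two places bear on who knows the arm. Section 2.4 states that "it is impossible to blind the operating physician" and that "the efficacy evaluator is a third party independent of the treatment operation and grouping". Section 2.5.2 confirms that in the sham arm "the acupuncturist will affix the placebo acupuncture device", so the operator handles the arm-specific device directly. Under 2.5 each patient stays with one acupuncturist for the whole course of 20 sessions.

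**The concern.** A harms comparison against sham is informative only if an event of a given kind is equally likely to be written down in either arm. A recording rule defined by cause puts that at risk, because somebody has to link the event to acupuncture before the form clearly applies.

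The examples add to the difficulty. Bleeding, broken needle, subcutaneous hematoma and infection belong chiefly to a needle that enters the skin. Section 2.5 describes the sham base as closed by a bonding layer and used with a flat-head needle, so these events will rarely arise there. Fainting is the only example that fits both arms equally well.

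Events that could occur in either arm, such as dizziness, headache, a fall or a skin reaction under the adhesive base, are not named. A site that reads the sentence literally could enter them when a real needle was used and leave them out when it was not, or the reverse. An event that is never entered is hard to recover later, so the wording matters before data collection is complete.

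**Working it through.** The article states no adverse event rate and no safety power figure, so there is no planned number to reproduce. The check is a comparison of the texts.

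**1. Scope of each statement**

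| Place | Activity | Limited by cause? |
|---|---|---|
| 2.7, first sentence | Handling, and recording on the form | Yes, tied to acupuncture |
| 2.7, serious events | Report to the ethics committee | No |
| 2.7, last sentence | Classification and reporting | No |
| Table 2 | Collection at weeks 1 to 5 and 25 | No |

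The recording statement is the narrowest of the four, yet classification and reporting draw on what has been recorded. If recording is narrow, the all-events promise cannot be met. If recording is meant to be broad, the first sentence is worded wrongly. Either way the section needs reconciling. Serious events have a reporting route without a cause qualifier, so the exposure is mainly to non-serious events.

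**2. The week 25 entry**

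Treatment ends at week 5, so the last collection point is 25 − 5 = 20 weeks after it. Few events that late would be put down to a needle. The row makes most sense under all-cause recording, which the first sentence of 2.7 does not provide.

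**3. Knowledge of the arm**

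- Operating physician: unblinded (2.4; repeated as a limitation in section 3).
- Participants: blinded (2.4).
- Independent third party: described for efficacy evaluation (2.4).
- Person who elicits, records or attributes adverse events: not named.

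An unblinded influence on attribution is therefore possible but not established.

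**4. What follows for the comparison**

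Let p be a true event risk that is the same in both arms, and let r₁ and r₀ be the probabilities that such an event is recorded in the acupuncture and sham arms. The recorded risk difference is

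p·r₁ − p·r₀ = p(r₁ − r₀).

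This is zero when r₁ = r₀, positive when r₁ > r₀ and negative when r₁ < r₀. The article supplies none of p, r₁ and r₀. Purely to show how open the answer is, take assumed values of p from 10% to 30%:

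- r₁ = 0.9, r₀ = 0.5: +4 to +12 percentage points (0.10 × 0.4 to 0.30 × 0.4).
- r₁ = 0.9, r₀ = 0.7: +2 to +6 points.
- r₁ = 0.5, r₀ = 0.9: −4 to −12 points.
- r₁ = r₀: 0.

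These values show only that the sign and size depend entirely on unknown inputs. They are not evidence that this trial's comparison will be wrong by any amount.

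**The case against.** The strongest reply is that the first sentence of 2.7 need not be restrictive. It contains no word such as only, its list is introduced as examples, and it can be read as describing the expected procedural events. The last sentence of 2.7 and Table 2 both point to all events. On that reading nothing is lost and only a phrase is loose.

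Three stronger readings are tempting, and the document supports none of them:

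- **That an event is recorded only after being judged to be caused by acupuncture.** No prior causality judgement is prescribed. The open list removes any limit to the five examples, although the qualifier on cause remains.
- **That the unblinded acupuncturist records or attributes the events.** No section says so. Section 2.9 has the assessor and the subject sign the case report form, but does not say whether the adverse event form is part of it. The inference is reasonable for events during a session, but it remains an inference.
- **That the safety comparison is biased.** With equal capture there is no bias, and with unequal capture the sign could go either way.

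Two further points stand. Motor worsening would not simply vanish, since UPDRSIII is measured in both arms at weeks 0, 5 and 25. And a journal article may leave to the full protocol who fills in the form, what any checklist contains and how safety tables are ranked. The absence of those details is not held against the plan here.

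What the reply does not remove is the mismatch. The benign reading relies on the other two statements to override the only sentence that says what goes on the form.

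**Conclusion.** The point holds as an inconsistency of scope with a possible consequence. Section 2.7 ties recording to acupuncture-related events, while its own last sentence and Table 2 cover adverse events without limit. Taken literally, the recording sentence makes capture depend on attribution in a trial where the operator knows the arm and a blinded independent role is stated for efficacy only. Capture could then differ between arms, and the comparison with sham could be biased.

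The consequence rests on two assumptions: that sites follow the recording sentence as written, and that attribution is made with some knowledge of the arm. Direction and size cannot be derived from the document. The primary MoCA analysis and the sample size are not affected. The change should be made, because safety is a stated aim, the correction is cheap, and missed events are hard to recover.

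**What to change.** In 2.7, replace the cause-limited recording sentence with a statement that:

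1. every untoward event from the first session on is recorded in both arms, regardless of suspected cause, with the present examples kept as illustrations;
2. participants in both arms are asked about events in the same way at the existing Table 2 time points;
3. relatedness to the procedure is graded afterwards in a separate field, where possible by the assessor who is already independent of treatment and grouping;
4. all-cause events are compared by arm.

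One precaution on item 3: needle-type events such as a hematoma may hint at the arm. The assessor should grade relatedness only after that patient's outcome scales are complete, so that blinding of the MoCA is not put at risk.

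The cost is a short rewording of 2.7, a relatedness field on the form and somewhat more recording at visits that already exist. The downside is that more unrelated events will be listed. No visit is added, and neither the sample size nor the handling of patients changes.
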